**Figure 1 figure1:**
[figure not shown]
Flowchart for participant recruitment in this study. Ease Online: Ease Anxiety in Social Event Online.

### Intervention: the Ease Online Program

The Ease Online program is 14 weeks in duration. The program adopts a blended mode of service delivery as guided self-help iCBT has demonstrated lower attrition than nonguided self-help iCBT [18], and therapist contact has been found to be a significant predictor of retention and outcomes [23]. The program consists of 9 web-based modules and 5 individual counseling sessions (including 2 VRET sessions). The program contents were developed on the basis of the CBT model developed by Beck [44] and CBT delivered to Chinese clients by Wong [45] and Pan and Zhuang [46]. Specifically, a variety of cognitive behavioral skills for coping with social anxiety are introduced in the 9 web-based modules, each with a specific theme. The themes of the nine web-based modules are (1) recognizing your social anxiety responses, (2) identifying automatic thoughts and cognitive distortions, (3) self-talk and positive statements, (4) behavioral experiment, (5) fear hierarchy, (6) exposure therapy, (7) identifying cognitive rules, (8) relaxing dysfunctional cognitive rules, and (9) saying bye-bye to social anxiety. The CBT skills are briefed and debriefed by using an animation video and demonstrated through 4 case videos. Each web-based module starts with a mood check for social anxiety in the past week and ends with a session review and an assignment that helps clients to apply the learned skills to cope with their own social anxiety. Other components of the program include therapist feedback on assignments, internal messages, forums, client portfolios, web-based questionnaires, reminders, and web-based bookings. An introduction video of the program provides a navigation on all of the program components after the clients log into the system. The client platform has a web-based version in which clients can log into the program website or a mobile app that can be downloaded through Google Play or Apple Store. After being randomized into the program, clients were provided an account to log into the system. Clients who are assigned a PC web account cannot log in through the app and vice versa. All clients were assigned to a therapist who not only provided web-based feedback on their assignments and responded to their private messages, but also offered 5 individual counseling sessions that monitored the progress of the clients and addressed any challenges that the clients encountered when working on the web-based modules. There is also a backstage management platform for the therapist, which offers different functions including creating cohorts, managing bookings and forums, providing feedback on client exercises, monitoring client progress, etc. The therapist helped the clients understand and review the module contents and apply the CBT skills into their own situations in 5 individual counseling sessions that were conducted either in person or on Zoom or WhatsApp.

A VR system for exposure therapy has also been developed for this program, which includes 5 virtual scenarios: (1) interviewing for a job, (2) delivering a presentation, (3) participating in work performance evaluation, (4) expressing disagreement, and (5) drinking in public. The VR system uses an 180° video of real humans. There is a storyline for each VR scenario and a couple of interactions between the client and the VR environment, which are guided by a prerecorded voice-over. The clients wear a head-mounted display and respond by moving their head. The voice responses of the clients are recorded in the VR system for replay. The technologies used for the development of the VR system include voice recording, VR180 stitching, VR game engine development, VR motion tracking on the target point, and an auto-trigger based on the user’s headset direction. An administration control panel has been developed for the therapist to control the VR interaction. In the beginning of each VRET session, the therapist provides a short briefing and asks the client to choose one VR scenario. Then, the client participates in the VRET for no longer than 15 minutes. The therapist then proceeds to debrief the client upon completion of each VRET session and submits a session report on the Ease Online system. Examples of VRET photographs are shown in Figure 2.

The program sessions outlined in Table 2 are released to the client on a weekly basis. The treatment schedule is programmed into the Ease Online system. Progress is recorded as a score when the client completes a task, and a total score is calculated as the total progress. All of the program videos are tailored for Hong Kong people and developed from local cases. The Cantonese language is used in the program. To ensure data security and privacy, 2-factor authentication is adopted when logging in with a password that is preset by the user and a one-time password sent to his/her email address. All of the collected electronic data are encrypted. The program is hosted on the server of the Information and Technology Office of the university where the author is employed. Before the program launched, a user acceptance test was conducted by the author and project staff, and bugs were fixed accordingly by the programmer of this project.

**Figure 2 figure2:**
[figure not shown]
Examples of images in virtual reality exposure therapy. (A) Client wearing a head mounted display. (B) Control panel of the VR system. (C) Virtual scenario of work performance appraisal. (D) Virtual scenario of expressing disagreement. VR: virtual reality.

**Table 2 table2:** Structure and content of the Ease Anxiety in Social Event Online program.

Week	Session	Mode	Theme
0	F0	F2F^a^	Intake interview
1	1	Web– or app–based	Recognizing your social anxiety responses
2	2	Web– or app–based	Identifying automatic thoughts and cognitive distortions
3	3	Web– or app–based	Self-talk and positive statements
4	F1	F2F	Counseling session (1)
5	4	Web– or app–based	Behavioral experiment
6	5	Web– or app–based	Fear hierarchy
7	6	Web– or app–based	Exposure therapy
8	F2	F2F	Counseling session (2)
9	F3	F2F	VR^b^ exposure therapy (1)
10	F4	F2F	VR exposure therapy (2)
11	7	Web– or app–based	Identifying cognitive rules
12	8	Web– or app–based	Relaxing dysfunctional cognitive rules
13	9	Web– or app–based	Saying bye-bye to social anxiety
14	F5	F2F	Counseling session (3)

^a^F2F: face-to-face session (in-person or on Zoom/WhatsApp).

^b^VR: virtual reality.

### Therapist Credibility

The therapist for the Ease Online program has a master’s degree in counseling (clinical mental health) and is registered as a certified counselor in both the United States and Canada. She has 9 years of counseling experience in Hong Kong. The intake worker is a registered social worker in Hong Kong who has a bachelor’s and a master’s degree in social work and counseling experience that spans more than 30 years in a variety of settings. The intake interviews were conducted by both the therapist and the intake worker, and all the service and initial screenings were delivered and conducted by the therapist—both are native Cantonese speakers.

### Compliance With the Intervention

Several strategies were adopted to ensure compliance with the intervention: (1) progress reports were completed and submitted by the therapist after each individual counseling session to record the understanding of the clients of the web-based modules and their difficulties in learning them, and applying CBT skills to cope with their own social anxiety; (2) the therapist completed and submitted a progress report in the system after each VRET session to record the session contents, including the VRET experience of the client, skills that the clients have learned to cope with social anxiety, and client feedback; the VRET process was recorded for debriefing in each VRET session; and (3) all the tasks completed by the clients were recorded in the system. A reward score was assigned to clients when they completed a task. Clients were provided a program workbook as an incentive if they completed 80% of the intervention contents.

### Outcome Measures

#### Primary Outcome Measures

The Chinese version of the SPIN [37,47] was used to assess the severity of social phobia symptoms. The measure consists of 17 items with 3 subscales: fear, avoidance, and physiological response. Participants were asked to rate their distress for each symptom during the past week on a 5-point Likert scale that ranges from “0” (not at all) to “4” (very much so). All of the item scores were summed up into a total score that ranged from 0 to 68, with a higher score indicating a higher level of anxiety. Sample items included “fear of others watching,” “avoid talking to others,” and “feeling bothered by blushing.” The α coefficient is .89 for the Chinese version of the SPIN [37].

#### Secondary Outcome Measures

The C-BAI [48,49] was used to measure the cognitive and somatic symptoms of anxiety. Participants were asked to rate 21 items on a 4-point Likert scale. Item scores were summed, with a higher total score indicating a higher level of anxiety. Sample items included “unable to relax” and “heart pounding or racing.” The α coefficient is .95 for the C-BAI [49].

The Chinese version of the BDI-II [39,50] was used to measure depressive symptoms. Participants were asked to rate 21 items on a 4-point Likert scale. The item scores were summed, with a higher total score indicating a higher level of depression. Sample items included “sadness” and “loss of pleasure.” The α coefficient is .86 for the Chinese version of the BDI-II [50].

The Chinese version of the General Health Questionnaire-12 [51] was adopted to evaluate psychological distress. The 0-0-1-1 scoring method was used to calculate the scale score (which ranged from 0 to 12), with higher scores indicating higher levels of psychological distress. The Cronbach α is .87 in a Hong Kong Chinese sample [52].

The Chinese Automatic Thoughts Questionnaire [53] contains 14 items for assessing positive and negative automatic thoughts. Participants were asked to rate the frequency of each thought in the past week on a 5-point Likert scale (which ranged from 1=“not at all” to 5=“all the time”). Item scores were summed up as the 2 subscale scores, with higher scores indicating more positive and negative automatic thoughts, respectively. Sample items included “I am worthless” and “No matter what happens, I know I’ll make it.” The Cronbach α is .83 in a Hong Kong Chinese sample [53].

The Chinese adaptation of the abbreviated version of the World Health Organization Quality of life Scale [54] was used to assess quality of life. This measure consists of 28 items, including 2 items that measure the overall quality of life and 26 items that measure physical and psychological health, social relationships, and the environment. Each item was rated on a 5-point Likert scale that ranged from 1=“very dissatisfied” to 5=“very satisfied,” with a higher score indicating better quality of life. The Cronbach α ranges from .59 to .78 and test-retest reliability ranges from 0.72 to 0.83 for this scale [54].

The Chinese version of the Internalized Stigma of Mental Illness scale [55,56] was used to evaluate the subjective experiences of self-stigma on mental illness. The measure consists of 24 items and 4 subscales: shame or alienation, stereotype endorsement, perceived discrimination, and social withdrawal. Participants were asked to rate items on a 4-point Likert scale that ranged from 1=“strongly disagree” to 4=“strongly agree.” All items were averaged as a scale score, with a higher score indicating a higher level of self-stigma. The Cronbach α is .93 in a Hong Kong Chinese sample [56].

In addition, before and after each VRET session, physical arousal through heart rate and blood oxygen levels were measured with a smart watch that the clients wore on their wrist.

### Ethical Considerations

Ethics approval was granted by the Human Research Ethics Committee (REC/18-19/0241) of the Hong Kong Baptist University. Participation in this study is voluntary and free of charge. Participants could withdraw at any time without any repercussions. High-risk cases identified at the screening stage were referred to local nongovernmental organizations or governmental social service sectors upon the consent of the applicant. Each participant was assigned a code number for identification in the program database to protect their privacy and anonymity.

### Data Analysis

Intent-to-treat analysis, which is the least biased way to estimate an intervention’s effects [57], was used for data analysis. Missing data will be managed using multiple imputation [58]. Multivariate ANOVA with repeated measures will be performed to test the intervention’s effectiveness on continuous variables over time. Time (pretest, posttest, and 3- and 6-month follow-ups), condition (web-based iCBT, app-based iCBT, and WLC), and the interaction of time-by-condition will be specified as the categorical fixed factors. Medication and demographic factors (eg, gender, age, and marital status) will be specified as fixed covariates to control the potential confounding effects. Cohen *d* will be calculated as the index of the effect size both within and between groups.

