**Methods:**

The 14-week Ease Online program is a guided self-help iCBT program with a blended mode of service delivery. The program comprises 9 web-based modules and 5 individual counseling sessions (including 2 VRET sessions) conducted remotely or face-to-face with a therapist to provide therapist support, as guided iCBT shows superior effects than unguided iCBT. Other program components include therapist feedback on assignments, internal messages, forums, client portfolios, web-based questionnaires, reminders, and web-based bookings. The program can be accessed either through a mobile app or program website through a PC with an internet connection. The participants are openly recruited and screened using a questionnaire and through an intake interview. Eligible participants are randomized by placing them into a web-based iCBT group, app-based iCBT group, or a waitlist control (WLC) group. Participants in the WLC group are assigned to the app-based program upon completion of the service of the 2 experimental groups. Measurements of social anxiety, depression and anxiety symptoms, psychological distress, automatic thoughts, and quality of life are administered at pretest, posttest, and 3- and 6-month follow-ups. Multivariate ANOVA with repeated measures will be performed to determine the intervention effectiveness on the continuous variables over time.

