### Sample Size

The sample size was calculated by using a computer program called G*Power (version 3.1.5; Universität Düsseldorf). The statistical method used was a multivariate ANOVA with repeated measures (within-between interactions). The effect size was assumed to be 0.40 (large) [40]. The number of groups was 3 (2 experimental groups and 1 control group) and 7 measures applied (please see the *Outcome Measures* section). The α value was set at .01. The calculations resulted in a minimum sample size of 139. This study aims at recruiting 330 eligible participants, with 110 in each experimental group and the waitlist control (WLC) group, respectively.

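### A significant result on the stated omnibus repeated-measures MANOVA would not show that Ease Online beat waiting on SPIN, the only primary outcome

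*Protocol article*

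**What the plan says.** Under Primary Outcome Measures there is one scale: "The Chinese version of the SPIN [37,47] was used to assess the severity of social phobia symptoms". Six further scales follow under Secondary Outcome Measures.

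The Data Analysis section does not carry that ranking through. It says "Multivariate ANOVA with repeated measures will be performed to test the" programme's effectiveness on continuous variables, in the plural. Time has four levels and condition has three, and "the interaction of time-by-condition will be specified as the categorical fixed factors". The abstract repeats the plan: "Multivariate ANOVA with repeated measures will be performed to determine the intervention effectiveness on the continuous variables over time". Between-arm differences appear otherwise only as Cohen *d*, which "will be calculated as the index of the effect size both within and between groups". That is an estimate and not a test. No SPIN comparison against waitlist and no deciding occasion is named.

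The Sample Size section uses the same family of test: "The statistical method used was a multivariate ANOVA with repeated measures (within-between interactions", with three groups, seven measures (cross-referenced to Outcome Measures), alpha .01 and a minimum of 139. The target is 330, or 110 per arm.

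The Research Design section and its Table 1 show the waitlist arm receiving the app programme straight after the experimental arms finish. Pretest to posttest is therefore the only interval in which waitlist is untreated.

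**The concern.** The trial's question is whether Ease Online lowers social anxiety compared with waiting. That is a directed comparison on one scale over one interval. The stated test asks instead whether anything differs among three arms across four occasions, and possibly across seven scales. Rejecting that hypothesis does not say which outcome, arm or occasion is responsible.

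Two errors are possible. Effectiveness could be claimed when neither programme, or only one, beat waiting on SPIN. Or, after a significant omnibus result, the supporting outcome, arm and occasion could be picked once the data are seen.

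**Working it through.** **1. The plan's own figure.** Inputs from Sample Size: effect size 0.40 (read as G*Power's f(V)), k = 3 groups, m = 7 measures, alpha = .01. For the within-between interaction with Pillai's trace:

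- s = min(k−1, m−1) = 2
- df1 = (k−1)(m−1) = 2 × 6 = 12
- df2 = s(N − k − (m−1) + s)
- noncentrality = f(V)² × s × N = 0.16 × 2 × N

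Power is 0.9898 at N = 138 and 0.9904 at N = 139, so 139 reproduces at a power of 0.99, which the article does not state. With m = 4 (the number of occasions) the same power needs 114. The count of seven scales therefore went into the calculation. At N = 330 power on these inputs exceeds 0.999.

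**2. What a rejection can mean if the scales are tested jointly.** Simulated case: seven outcomes at one time point, Pillai, alpha .01, between-outcome correlation 0.5 (assumed). There is no effect on SPIN and d = 0.5 on the other six scales in both programmes. The omnibus rejects in over 99% of runs at 110 per arm and in about 68% at 46 per arm.

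**3. What a rejection can mean if SPIN is tested on its own.** The time-by-condition test has (3−1)(4−1) = 6 degrees of freedom. Simulated with Pillai, alpha .01, 110 per arm, correlation 0.5 between occasions (assumed), 3,000 runs:

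| True pattern on SPIN | Rejections |
|---|---|
| No arm differs at posttest; waitlist differs by 0.5 SD at the two follow-ups only | 99% |
| Web differs by 0.5 SD from app and waitlist; app equals waitlist | 95% |

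In the first row there is no effect against an untreated control. In the second, one programme does nothing. Both rates fall with smaller differences or fewer participants. They illustrate the problem and do not forecast this trial's result.

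**4. Does a focused contrast gain power?** Assumed: d = 0.4 in both programmes, pretest-posttest correlation ρ = 0.5, two-sided alpha .01 (critical z = 2.576), 110 per arm, normal approximation for the contrasts. Power = Φ(d/SE − 2.576), where SE² = v × (sum of 1/n). For change scores v = 2(1−ρ) = 1; with pretest adjustment v = 1−ρ² = 0.75.

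| Test on SPIN | SE | Power |
|---|---|---|
| 6-df interaction, four occasions | – | 0.75 (F approximation); about 0.73 simulated |
| 2-df interaction, pretest-posttest change | – | 0.70 |
| One programme vs waitlist, change | √(2/110) = 0.135 | 0.65 |
| Pooled programmes vs waitlist, change | √(1/220 + 1/110) = 0.117 | 0.80 |
| One programme vs waitlist, adjusted | √(0.75 × 2/110) = 0.117 | 0.80 |
| Same, at the first Holm threshold .005 | 0.117 | 0.73 |
| Pooled vs waitlist, adjusted | √(0.75 × (1/220 + 1/110)) = 0.101 | 0.92 |

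Cutting degrees of freedom alone gains nothing here (0.70 and 0.65 against 0.75). The gain comes from pretest adjustment or from pooling. With an assumed 55 analysable per arm, the 6-df test has 0.33, the adjusted single-arm contrast 0.44 and the adjusted pooled contrast 0.59.

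The document gives no SPIN effect or SD, so *d* has to be varied. Without the adjustment gain (v = 1), at 110 per arm and d = 0.3 / 0.4 / 0.5 / 0.8, power is 0.50 / 0.80 / 0.96 / above 0.99 pooled and 0.36 / 0.65 / 0.87 / above 0.99 for one programme.

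**The case against.** **The article never says that all scales enter one model.** This is right. The Data Analysis wording also fits the multivariate approach to repeated measures run scale by scale, and SPIN would then have its own interaction test. The sample-size formula does not settle it: 12 degrees of freedom describes one variable at seven occasions, whereas a joint test of seven scales, four occasions and three arms would have 7 × 3 × 2 = 42. A reader might infer that SPIN has no test of its own, but the text does not support that as a certainty. The point survives because step 3 above uses the scale-by-scale reading.

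**Web versus app and the follow-ups are legitimate questions.** They are. The two platforms are randomised and the follow-ups are planned. It would be wrong to say that power is spread over contrasts nobody asked about. What stands is that they are bundled into the test that carries the effectiveness claim.

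**A power loss is not shown.** This also stands. On the plan's own inputs there is no shortfall, and step 4 shows that fewer degrees of freedom do not help by themselves. A seven-outcome omnibus can gain or lose. With d = 0.5 on SPIN alone and 110 per arm, it has 0.56 against 0.91 for a SPIN-only three-arm test at between-outcome correlation 0, but above 0.99 against 0.91 at correlation 0.7.

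**Contrasts and their order belong in the SAP.** In part. A condensed article may leave Holm steps and a primary occasion to the SAP, and their absence alone would not be a finding. But the article does more than omit detail: in two places it fixes the test by which effectiveness will be judged, and that test does not match its own primary outcome.

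**Conclusion.** The concern holds as a matter of interpretation: the stated effectiveness test cannot be read as an answer about SPIN against waiting, on either reading of the Data Analysis section. This follows from the hypothesis tested and from the waitlist arm's later treatment, both of which are in the text. The 99% and 95% rejection rates show that the gap can matter at the planned size; they rest on assumed differences of 0.5 SD and a correlation of 0.5.

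A reader might go further and conclude that the omnibus wastes power or that the trial is too small. The documents do not support either. Any power advantage of the focused contrast depends on pretest adjustment or pooling and on an assumed *d* and correlation. The change should be made before the analysis; the article reports data collection as still ongoing.

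**What to change.** In Data Analysis and the abstract, base the effectiveness claim on SPIN from pretest to posttest, programme versus waitlist, adjusted for pretest SPIN, at the planned alpha of .01. Test web versus waitlist and app versus waitlist under multiplicity control such as Holm. A pooled-programmes contrast as the first step is one option; it is a preference, since it averages two delivery modes that the design keeps apart.

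Report web versus app as a separate estimate with a confidence interval. Label the MANOVA, the other six scales and the 3- and 6-month occasions as secondary, and state whether the scales are analysed jointly or singly.

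The cost is analysis wording only: no new data and no change to sample size or conduct. The downside is that no single multivariate P value carries the claim.

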### Research Design

Although deterioration in a control condition can take place [42], Steinert et al [43] conducted a meta-analysis and found only small changes in the WLC groups during short-term wait periods for clients with SAD in RCTs. Thus, this study adopts a WLC group design to conduct a 3-arm RCT as shown in Table 1.

There were 2 experimental groups that joined either the web-based or app-based iCBT program (Ease Online). The WLC group received the app-based treatment immediately after the 2 experimental groups completed the program. All 3 groups completed the same web-based questionnaire at pretest, posttest, and 3- and 6-month follow-ups. The WLC group completed the questionnaire one more time at posttest after the 2 experimental groups completed the program. To increase the submission rate of questionnaire, participants were given 2 more weeks to submit an email questionnaire after the submission deadline in the program system. The RCT was conducted in cohorts for implementation feasibility. Specifically, in each cohort, around 30 qualified participants were randomized into one of the 3 groups through computer-generated random numbers, with approximately 10 in each group. The program evaluators were blinded to the allocation of the participants. The participant recruitment flowchart is shown in Figure 1.

**Table 1 table1:** Participant group design.

Groups	Research design						
Web-based	O^a^	X^b^	O		O	O	N/A^c^
App-based	O	X	O		O	O	N/A
Waitlist control	O		O	X	O	O	O

^a^O: test.

^b^X: intervention.

^c^N/A: not applicable.

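### The time-by-condition test keeps the waitlist arm as comparator at 3 and 6 months, when it is in or past its own treatment, so it cannot show a controlled lasting effect

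*Protocol article*

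**What the plan says.** The Data Analysis section states the purpose of the main test: "Multivariate ANOVA with repeated measures will be performed to test the intervention’s effectiveness on continuous variables over time". Its fixed factors are "Time (pretest, posttest, and 3- and 6-month follow-ups), condition (web-based iCBT, app-based iCBT, and WLC), and the interaction of time-by-condition", and Cohen d "will be calculated as the index of the effect size both within and between groups".

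Research Design states when the control arm is treated: "The WLC group received the app-based treatment immediately after the 2 experimental groups completed the program". The abstract agrees: "Participants in the WLC group are assigned to the app-based program upon completion of the service of the 2 experimental groups". Table 1 places the WLC intervention between that arm's second and third tests.

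On assessments, Research Design says "All 3 groups completed the same web-based questionnaire at pretest, posttest, and 3- and 6-month follow-ups", and adds "The WLC group completed the questionnaire one more time at posttest after the 2 experimental groups completed the program". Table 1 accordingly gives the WLC arm five tests and each programme arm four.

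**The concern.** A waitlist arm serves as control only while it waits. Once it has the app programme, comparing it with the programme arms compares treated with treated. The stated model nevertheless keeps WLC as a condition level at all four occasions and is described as the test of effectiveness over time. It neither limits the controlled comparison to posttest nor recodes WLC after it crosses to treatment.

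What is at stake is the claim of durability. If the programme works and its benefit lasts, the WLC arm should move towards the programme arms by the follow-up visits and the between-group d should shrink. A reader of the results could take that for a fading benefit. In the other direction, a significant omnibus interaction could be taken as proof of benefit to 6 months, when the signal may come from posttest, or from the WLC arm's own later improvement.

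**Working it through.** **Status of the WLC arm at each model occasion.** The programme lasts 14 weeks (Intervention section), and 3 months is about 52/4 = 13 weeks.

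| Occasion | Programme arms | WLC, calendar time | WLC, counted from its own treatment |
|---|---|---|---|
| Pretest | untreated | untreated | untreated |
| Posttest | treated | untreated (end of wait) | treated |
| 3 months | treated | about week 13 of 14, or just finished (Table 1 alignment) | treated |
| 6 months | treated | treated | treated |

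On neither reading is there an untreated comparator at 3 or 6 months. On the calendar reading, posttest is properly controlled.

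**The plan's own sample-size figure.** Sample Size gives 3 groups, 7 measures, effect size 0.40, alpha .01 and a minimum of 139, with no power stated. The repeated-measures MANOVA interaction (Pillai, noncentral F) has s = min(2, 6) = 2, df1 = 2 × 6 = 12, df2 = s(N − 3 − 6 + s) and noncentrality λ = s·N·f². At an assumed power of 0.99, the smallest N is 139, so the figure reproduces. It concerns the omnibus interaction and does not bear on who is untreated when.

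**What the follow-up visits can show.** The documents give no expected SPIN difference and no correlation between occasions. Assume d = 0.4, 0.5 or 0.8, correlation 0.5, 110 per arm (Sample Size) and alpha .01. Let the benefit last fully and WLC reach the same level once treated. Means in SD units at pretest, posttest, 3 and 6 months are:

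- programme arms: (0, −d, −d, −d)
- WLC: (0, 0, −d, −d)

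The between-group d is then d at posttest and 0 at both follow-ups. On pretest plus the two follow-ups, all three arms have the same mean change, so the noncentrality is 0 and the rejection rate equals alpha, whatever d or the correlation. Simulation of the Pillai test (3,000 runs) agrees:

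| d | WLC treated after posttest | WLC hypothetically untreated |
|---|---|---|
| 0.4 | 0.9% | 75.8% |
| 0.5 | 1.1% | 94.5% |
| 0.8 | 0.7% | 100% |

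If WLC catches up only by a fraction c, the follow-up difference is d(1 − c). For d = 0.5 this is 0.25, 0.125 and 0 at c = 0.5, 0.75 and 1. It then measures incomplete catch-up, not persistence.

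**What the omnibus test can show.** At d = 0.5, the four-occasion test rejects 93.3% of the time when the benefit lasts. It rejects 100% when the benefit vanishes after posttest and WLC has its own short-lived gain at 3 months. A small P value does not separate the two. With no effect at all it rejects 1.3%, close to its alpha.

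**What remains at posttest.** With correlation 0.5, the SD of change is √(2 × (1 − 0.5)) = 1. The three-arm pretest-posttest noncentrality is 110 × (2/3) × d², or 18.3 at d = 0.5, giving power of about 91% (about 70% at d = 0.4, above 99.9% at d = 0.8). For a single programme arm against WLC at alpha .01, power is 65%, 87% and above 99.9% at d = 0.4, 0.5 and 0.8. If the plan's own effect size of 0.40 is carried over to two occasions, λ = 330 × 0.16 = 52.8 and power exceeds 99.9%. All of these are before missing data.

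**The case against.** The strongest reply is that the randomised contrast against an untreated arm does sit inside the interaction. On the calendar reading, pretest to posttest is fully controlled, the omnibus test holds its alpha when nothing works, and a significant result is evidence of some effect. The stated rationale for the waitlist refers only to short waits, which suggests the controlled comparison was meant for that period. Web versus app is randomised at every visit, so keeping three conditions and the follow-ups in one model has a legitimate use. The article does not say at which visits, or between which arms, d will be computed. All of this stands, and it limits the point to the follow-up visits.

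Three stronger readings are tempting and are not supported:

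- A reader might infer that the test shows no controlled effect at all, or that its conclusion would be wrong in either direction. Neither holds at posttest. An error arises only if the omnibus P value or a follow-up d against WLC is read as controlled maintenance.
- A reader might infer that the end-of-wait WLC test is left out, so that the whole interaction rejects at only 1%. The sentence about the extra WLC questionnaire is ambiguous, but nowhere is that test said to be dropped. A condensed article may also leave the mapping of tests to a fuller document, so its absence is not itself the fault.
- A reader might infer that the omnibus test is always equally powerful whether WLC catches up or is never treated. At d = 0.5 and correlation 0.5, both noncentralities are 27.5 under compound symmetry. Under a first-order autoregressive correlation they are 29.5 and 20.4. Only the qualitative point is general.

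**Conclusion.** The concern holds for 3 and 6 months. The article itself names the occasions, the conditions and the purpose of the test, so this is a stated analysis that can mislead and not a detail left to another document. No controlled statement about lasting benefit can come from the omnibus interaction or from a d against WLC at those visits. Under full catch-up, a lasting benefit is detected there at the alpha rate, about 1%. That figure rests on the WLC arm reaching the programme arms' level by the follow-up visits. The hypothetical 76% to 100% also rests on the assumed d and correlation. The posttest comparison is sound if the end-of-wait WLC test fills the posttest level.

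**What to change.** - Prespecify the controlled comparison as each programme arm versus WLC on SPIN at the end-of-wait posttest, before waitlist treatment starts. A separate model or a planned contrast within the same model would both serve.
- Make no comparison with WLC, by test or by d, at 3 and 6 months. Use those visits for web versus app and for within-arm description, and state that maintenance is uncontrolled.
- State how the five WLC tests map to the model's time levels, with the end-of-wait test as posttest. Report the later WLC tests separately as a delayed-treatment replication.

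This changes analysis wording only and needs no new data. The price is that the controlled claim narrows to posttest. Power for that contrast should be judged on the data actually obtained, since the Limitations section reports quite high missingness at posttest and follow-up.
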